### Therapists

All therapists are certified clinical psychologists, with a broad experience in treating refugee children and families and sufficient training in both active treatment conditions. Each therapist received a 4-day basic training on NET by official NET trainers and additionally must have completed a minimum of one full KIDNET treatment under supervision. In addition, each therapist giving treatment in this study received a 9-day training level 1 and level 2 according to the standards of EMDR Europe.

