### Procedure

When a child is identified as a potential participant an introductory meeting is planned with the caregiver(s), the child, a member of the research team, and, if needed, an intercultural mediator. An Eritrean and Syrian intercultural mediator are part of the research team. In addition to translation/interpretation, it is expected that they may increase the trust of the participants by sharing their cultural background, can explain the study in their native language, and discuss stigma related to the use of mental healthcare. The second meeting, after obtaining informed consent, consists of further intake questions and collecting T1 data. When the CAPS-CA-5 has been administered and when the participant meets the inclusion criteria, a participant number is assigned. Then, the therapist is chosen based on availability. Hereafter, the participant will be randomly assigned to the EMDR condition, KIDNET condition, or the waitlist control group. In this way, randomization will occur across therapists. In case of a treatment condition (EMDR or KIDNET), the first session starts within 4 weeks after T1. In the case of a crisis, a child psychiatrist is available for consultation—as is a normal procedure during treatment.

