#### Informed consent, randomization, and blinding

During the intake, the assessor explains the aim, method, benefits, and potential hazards of the study. The child and his/her legal guardian will then receive the informed consent (also available in Arabic and English). When the child (12 years and older) and his/her legal guardian agree to participate, the assessor obtains informed consent. When a child meets the inclusion criteria, an independent colleague of ARQ Centrum’45 is contacted and uses random allocation software for the random allocation of the participants to EMDR, KIDNET, or the waitlist control group. Random allocation is performed using a randomized block design with variable block sizes and an allocation ratio of 1:1:1. After the allocation is known, the independent colleague will inform the research coordinator. Hereafter, the research coordinator will inform the therapist about the allocation. Neither therapists nor study participants can be blinded to the treatment condition given the nature of the interventions. Independent members of the research team will administer T1–T4 assessments and remain blinded to the two treatment allocations (EMDR and KIDNET). Statistical analyzes will not start until the final assessment has been done. Hereafter, data analysts will no longer be blinded for the treatment allocation.

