#### Waitlist control group

The aim of the current trial is to evaluate the effectiveness of KIDNET and EMDR treatment. Therefore a waitlist control group is chosen as a comparator. Once trauma-focused treatment has been indicated, a child may be assigned to the waitlist control group. When a participant is randomized to the waitlist control group, he or she will receive no trauma treatment for 8 weeks. This implies there will be no contact (except in case of emergency) for 8 weeks before the post waitlist measurements (T2) and then the start of either one of the treatment conditions (second randomization).

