### Statistical analyses

Descriptive statistics and analysis of variance will be performed. All three groups will be compared with regard to pre-treatment variables such as demographic variables (age, gender, ethnicity). To test the effectiveness of EMDR vs waitlist control group and KIDNET vs waitlist control group, analyses of variance will be performed with time (T1 and T2) as within-subject variable, and treatment (EMDR, KIDNET, or waitlist control group) as between-subject variable. To test the effectiveness of EMDR compared to KIDNET, analyses of variance will be performed with time (pre-treatment, post-treatment, and follow-up) as within-subject variable, and treatment (EMDR and KIDNET) as between-subject variable. Both analyses will be done twice; with per-protocol sets and intention-to-treat sets. SPSS will be used for multiple imputations techniques for missing data, the per-protocol analyses, and the intention-to-treat analyses. CONSORT criteria will be followed for the statistical analyses (and reporting) of randomized controlled trials. Repeated measures (per session) will be conducted to evaluate treatment progress (CRIES-13 child version).

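### The planned ANOVAs have no therapist term: if therapists differ, the standard error against waitlist is modestly too small, and EMDR v KIDNET mainly loses precision

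*Protocol article*

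**What the plan says.** All places are in the protocol article.

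- **Therapists:** all therapists have "sufficient training in both active treatment conditions".
- **Procedure:** once a child is found eligible and numbered, "Then, the therapist is chosen based on availability". Allocation follows, and the article adds: "In this way, randomization will occur across therapists".
- **Informed consent, randomization, and blinding:** "Random allocation is performed using a randomized block design with variable block sizes and an allocation ratio of 1:1:1". Stratification by therapist is not mentioned.
- **Waitlist control group:** "This implies there will be no contact (except in case of emergency) for 8 weeks" before T2.
- **Statistical analyses, therapy v waitlist:** time (T1, T2) within subjects and "treatment (EMDR, KIDNET, or waitlist control group) as between-subject variable".
- **Statistical analyses, EMDR v KIDNET:** three time points within subjects and "treatment (EMDR and KIDNET) as between-subject variable".

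Neither model names a therapist term. That each therapist delivers both methods is a strong inference from the Therapists and Procedure sections; the article does not say it outright.

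**The concern.** Children treated by the same therapist may have more alike outcomes than children treated by different therapists. An ANOVA with treatment as its only between-subject factor counts every child as independent.

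The consequence differs between the two comparisons.

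- **Therapy v waitlist (research questions 1 and 2).** At T2 the treated children share therapists, while the waitlisted children have not yet been treated by anyone. Clustering sits on one side only. It adds variance to the therapy mean that the ANOVA does not count, so p-values and intervals lean towards therapy.
- **EMDR v KIDNET (research question 3).** The therapist is fixed before individual allocation and crosses both treatments. Differences in general skill then behave like a baseline covariate left out of the model. They stay in the error term, although the design would allow them to be removed.

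**Working it through.** **Inputs from the article.** Sample size section: f = 0.20, correlation between assessments 0.40, power 0.80, alpha 0.05, 78 in total (26 per condition); 39 per treatment for EMDR v KIDNET (26 + 13 from the waitlist). **Assumed, because not stated:** K = 5 to 10 therapists; therapist share of variance (ICC) 0.05 to 0.10 in the analysed change score; equal total variance in each arm.

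**1. The plan's own figure.** For the group-by-time interaction with 3 groups and 2 times, lambda = f² × N × 2 / (1 − rho) = 0.04 × 78 × 2 / 0.60 = 10.4, with 2 and 75 degrees of freedom. Power is 0.815, so 78 reproduces. The calculation has no allowance for therapist clustering.

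**2. Therapy v waitlist.** With n = 26 per arm and m = n/K treated children per therapist in an arm:

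true SE / ANOVA SE = sqrt[(2 + (m − 1) × ICC) / 2]

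The real two-sided type I error is the normal tail area beyond 1.96 divided by that ratio.

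| K | m | ICC | SE ratio | Type I error |
|---|---|---|---|---|
| 10 | 2.6 | 0.05 | sqrt(1.040) = 1.020 | 5.5% |
| 10 | 2.6 | 0.10 | sqrt(1.080) = 1.039 | 5.9% |
| 5 | 5.2 | 0.05 | sqrt(1.105) = 1.051 | 6.2% |
| 5 | 5.2 | 0.10 | sqrt(1.210) = 1.100 | 7.5% |

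A simulation of change scores with uneven caseloads (20,000 runs per setting, 26 per arm, 4 to 12 therapists, ICC 0.02 to 0.10) gave ratios of 1.01 to 1.15 and type I error of 5.2% to 8.5%.

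If the ICC is taken to refer to the T2 score instead, the change score has variance 2 × (1 − 0.40) = 1.2 units. The shares become 0.05/1.2 = 0.042 and 0.10/1.2 = 0.083. The ratios are then about 1.02 to 1.08 and the type I error about 5.4% to 7.1%.

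**3. EMDR v KIDNET, therapist effect common to both methods.** The same kind of simulation with 39 per arm gave ratios of 0.99 to 1.01 and type I error of 4.6% to 5.3%: the ANOVA standard error is valid. If arms were exactly balanced within therapist, the ratio would be sqrt(1 − ICC), which is 0.975 at 0.05 and 0.949 at 0.10, so the ANOVA would be slightly conservative. The loss is the 5% to 10% of variance that a therapist block could remove.

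**4. EMDR v KIDNET, treatment difference varying by therapist.** With a therapist-by-treatment variance share v, the ratio is sqrt[1 + (39/K − 1) × v]. For K = 10 and v = 0.02 it is sqrt(1.058) = 1.029 (type I error 5.7%). For K = 5 and v = 0.05 it is sqrt(1.34) = 1.158 (9.0%). Simulation over 4 to 12 therapists and v of 0.02 to 0.10 gave 1.03 to 1.42 (5.7% to 16.5%). These figures show only what such an interaction would do; nothing in the article indicates its size or that it exists.

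**The case against.** A reader might infer that the standard errors are wrong in both main comparisons. The article does not support that. Individual allocation after the therapist is chosen protects EMDR v KIDNET against therapist differences common to both methods (step 3). The absence of stratification by therapist does not change this, because chance imbalance under individual randomisation is already covered by the ANOVA standard error.

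A reader might also take the training rules as evidence that therapists differ in relative skill: 4 days for KIDNET, after which each therapist "must have completed a minimum of one full KIDNET treatment under supervision", against 9 days for EMDR. The Therapists section sets these rules for every therapist. They describe a difference between the methods, not between therapists. Supervision with video every 6 weeks and fidelity checks work against therapist-specific differences.

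Putting 31 per arm into step 2 gives a larger inflation, 3% to 12%. But 31 is the number before attrition, whereas the 39 used for the other comparison is after it. The like-for-like figure is 26.

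Other objections stand in part. The size rests wholly on an assumed number of therapists and ICC, so the waitlist finding is conditional on therapists differing. With 2.6 to 5.2 treated children per therapist and arm, a therapist variance will be poorly estimated. The article is condensed, and a therapist term could appear in a fuller plan. Against that, it does name a concrete model with its factors, and that model leaves out a feature the Procedure section builds in.

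**Conclusion.** The point holds in a limited form. Against waitlist, the stated ANOVA understates the standard error if therapists differ, in the direction that favours therapy. With 5 to 10 therapists, an ICC of 0.05 to 0.10 in the change score and 26 per arm, the true standard error is about 2% to 10% larger and a nominal 5% test runs at about 5.5% to 7.5%. For EMDR v KIDNET the standard error stays valid under therapist differences shared by both methods, and the cost is about 5% to 10% of removable variance on the same assumption. It would be too small only under a therapist-by-treatment interaction, on which the article gives no information. This is a modest improvement worth making, not a flaw that undermines the trial.

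**What to change.** **Therapy v waitlist.** Replace the plain ANOVA with a partially nested mixed model: a therapist effect in the therapy arms only, each waitlisted child standing alone, and small-sample degrees of freedom.

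**EMDR v KIDNET.** Add therapist as a blocking factor, using the therapist on record at the randomisation to EMDR or KIDNET. For waitlisted children, a third of this sample (26 of 78), the article does not say whether the therapist chosen at entry is kept. The plan should state that the therapist used is the one fixed before the second randomisation. Report therapist-by-treatment as a sensitivity analysis.

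**Cost.** A few lines of analysis wording, the therapist's identity for each child, and the mixed-model procedure in SPSS, which is already the planned software. Analyses do not start until the final assessment, so the change can be specified in advance. Intervals against waitlist become slightly wider, a few degrees of freedom are used, and the therapist variance will be imprecise if there are few therapists.

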### Objectives of the current trial

The aim of the current study is to investigate the efficacy of both EMDR and KIDNET compared to a waitlist control group. The research questions are:
Is EMDR effective in decreasing PTSD and posttraumatic stress symptoms, decreasing behavioral and emotional symptoms, and improving quality of life in refugee children and adolescents, compared to a waitlist control group?

We hypothesize that EMDR is more effective in reducing PTSD and posttraumatic stress symptoms, behavioral and emotional symptoms, and improving quality of life in refugee children and adolescents, compared to a waitlist control group.
2)Is KIDNET effective in decreasing PTSD and posttraumatic stress symptoms, decreasing behavioral and emotional symptoms, and improving quality of life in refugee children and adolescents compared to a waitlist control group?

We hypothesize that KIDNET is more effective in reducing PTSD and posttraumatic stress symptoms, behavioral and emotional symptoms, and improving quality of life in refugee children and adolescents, compared to a waitlist control group.
3)Is there a difference in effectivity between EMDR and KIDNET?

We hypothesize that both interventions (EMDR and KIDNET) are effective in reducing post-traumatic stress symptoms. Therefore, we do not expect (large) differences in effectiveness between the two interventions and hypothesize that both interventions equally reach efficacy in refugee children aged 8–18 years. However, this comparison has not been done before, in case there is a small difference in effectiveness, we aim to detect it.

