#### Sample size

Previous studies with refugee children show large between-group effect sizes for PTSD symptom severity for KIDNET vs control group and EMDR vs control group [18, 20, 21, 25]. Therefore, at least a medium effect size can be expected when comparing the two treatment conditions (EMDR and KIDNET) to the waitlist control group. With the following assumptions: a correlation between assessments of 0.40, a modest effect size of intervention (ES *f*=0.20), a power of .80, alpha of .05, and two groups (EMDR, KIDNET versus waitlist control group), a total sample of 78 participants will be needed (26 participants per condition), (G*power [49]).

We hypothesized that both interventions (EMDR and KIDNET) are effective in reducing post-traumatic stress symptoms. In case there is a small difference in effectiveness, we aim to detect it. Therefore, the number of participants needed to detect a small effect size (*f*=0.17) is computed, resulting in a preferable sample size of 78 participants (39 participants per treatment condition; EMDR and KIDNET).

After the waitlist period of 8 weeks, the second randomization will take place. Participants will be randomly assigned to EMDR or KIDNET which results in 13 extra participants in both treatments group and thereby a total of 39 participants in both treatment groups. Since a crossover design is not used, the data of the participants (*n*=26) who were secondly randomized into a treatment condition will only be used in the analyses of EMDR versus KIDNET. A conservative 20% attrition rate will be taken into account, resulting in a total required sample of 93 participants.

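### EMDR v KIDNET is compared by a three-occasion ANOVA that treats the pre-treatment score as an outcome; one baseline-adjusted comparison on the same data would be clearly more efficient and easier to read

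*Protocol article*

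**What the plan says.** All references are to the protocol article.

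- **Objectives of the current trial**, question 3: "Is there a difference in effectivity between EMDR and KIDNET". The text expects no large difference and wants a small one to be detectable. It names no time point.
- **Statistical analyses**: the head-to-head model is an analysis of variance "with time (pre-treatment, post-treatment, and follow-up) as within-subject variable, and treatment (EMDR and KIDNET) as between-subject variable". No interaction, contrast or deciding term is named. For the waitlist comparisons the model has two occasions only: "analyses of variance will be performed with time (T1 and T2) as within-subject variable".
- **Sample size**: for EMDR v KIDNET, "the number of participants needed to detect a small effect size" (f = 0.17) is computed, "resulting in a preferable sample size of 78 participants (39 participants per treatment condition; EMDR and KIDNET"). The effect tested and the number of occasions are not given. The preceding waitlist calculation assumes "a correlation between assessments of 0.40" and "a power of .80, alpha of .05, and two groups (EMDR, KIDNET versus waitlist control group").
- **Trial design**: post-treatment is 4 weeks, and follow-up 3 months, after the last session.
- **Abstract, Methods**: the primary outcome, CAPS-CA-5 diagnosis and severity, is placed at baseline and at both later assessments.

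**The concern.** With three occasions and two therapies, the treatment-by-time term has (3 − 1) × (2 − 1) = 2 degrees of freedom. Its null hypothesis is that both therapies have the same profile over all three occasions. A significant result does not by itself say which therapy did better, or when.

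Two features cost precision. A difference that is equal at both later occasions lies wholly in one degree of freedom, so the second one only raises the critical value. Also, the pre-treatment score, where randomised groups have no expected difference, is used as an outcome level. As a covariate it would remove variance.

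At stake is the trial's only head-to-head question, in a small sample, for an effect that the investigators themselves expect to be small or absent.

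**Working it through.** **Inputs.** n = 39 per therapy and f = 0.17 (Sample size). ρ = 0.40 and two-sided α = 0.05, carried over from the waitlist calculation (assumption). SD = 1 at each occasion. Equal correlations unless stated.

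**The plan's own figures first.** For a within-between interaction with k groups and m occasions, λ = f²Nm/(1 − ρ), with df (k − 1)(m − 1) and (N − k)(m − 1).
- Waitlist, f = 0.20: k = 3, m = 2 gives N = 78 for 80% power, as stated ("a total sample of 78 participants will be needed (26 participants per condition")). With k = 2 it gives 62. This supports treatment-by-time as the intended effect.
- EMDR v KIDNET, f = 0.17, k = 2: N = 70 with three occasions and 84 with two. The stated 78 is not reproduced without settings that the article does not give. That is a separate matter. At N = 78 with three occasions, λ = 0.0289 × 78 × 3/0.60 = 11.27 on (2, 152) df, and power is 85.4%.

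**What f = 0.17 means in SD.** For a lasting difference d, the between-therapy differences over the occasions are (0, d, d). Their centred sum of squares is 2d²/3, so λ = (n/2)(2d²/3)/(1 − ρ). Equating this with the formula above gives f² = d²/18, so d = 0.17 × √18 = 0.72 SD.

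**Four tests of the same data, lasting d = 0.5, n/2 = 19.5.**
- Interaction: λ = 19.5 × (2 × 0.25/3)/0.60 = 5.42 on (2, 152) df.
- Treatment main effect (mean over all three occasions): variance (1 + 2 × 0.40)/3 = 0.60 and difference 2d/3, so λ = 19.5 × 0.111/0.60 = 3.61 on (1, 76) df.
- Mean of the two later scores minus pre-treatment: variance 0.70 + 1 − 0.80 = 0.90, so λ = 19.5 × 0.25/0.90 = 5.42 on (1, 76) df.
- Mean of the two later scores adjusted for pre-treatment: variance 0.70 − 0.40² = 0.54, so λ = 19.5 × 0.25/0.54 = 9.03 on (1, 75) df.

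| Test | Power at 0.5 SD | Power at 0.72 SD | Difference for 80% power |
|---|---|---|---|
| Interaction, 2 df | 53% | 85% | 0.67 SD |
| Treatment main effect | 47% | 77% | 0.75 SD |
| Mean change, unadjusted | 63% | 91% | 0.61 SD |
| Mean, baseline-adjusted | 84% | 99% | 0.47 SD |

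**Where the gain comes from.** The interaction and the mean-change contrast share λ = 5.42, so the step between them is the cost of the second degree of freedom alone: 10 points at 0.5 SD and 6 points at 0.72 SD. The step from unadjusted to adjusted is 21 and 8 points.

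**Sensitivity: post-treatment and follow-up correlate 0.7 (assumption).** The variances become 0.85 + 1 − 0.80 = 1.05 and 0.85 − 0.16 = 0.69. At 0.5 SD the mean change has 57% power and the adjusted mean 75%. The interaction has about 54% with a sphericity correction and 46% in multivariate form.

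**A difference at post-treatment only.** The differences are (0, d, 0), and the centred sum of squares is again 2d²/3. Under equal correlations the interaction therefore has the same power as for a lasting difference, 53% at 0.5 SD. The adjusted mean sees d/2 = 0.25: λ = 19.5 × 0.0625/0.54 = 2.26, power 32%. With the 0.7 correlation it is 26%.

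**The case against.** **The article does not say that the interaction is the only test.** This stands. A reader might infer that one 2-df F test is the sole head-to-head result, with no estimate at either occasion. The text names the factors, not the term. The same model also yields a treatment main effect and occasion means, and an analysis plan that is not shown may set contrasts. What remains is that neither term of the stated model is efficient: the main effect averages in the pre-treatment score and does worse than the interaction.

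**The trial is not underpowered for its stated target.** This also stands. A reader might infer otherwise from the 53%, but 0.5 SD is not a figure in the article. At the planned f = 0.17 the interaction has about 85% power under sphericity. The smaller difference matters only because the objectives ask to detect a small one.

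**Reacting to a temporary difference is not an error.** Correct. It is tempting to call the ANOVA wrong because it can be significant when the therapies are equal at 3 months. But the primary outcome is placed at both later occasions, and question 3 is not limited to lasting differences. The averaged contrast also rejects in 26–32% of trials for a 0.5 SD difference that is gone by follow-up. It lessens this behaviour and does not remove it.

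**A single contrast is not automatically better.** True. Under equal correlations a plain follow-up-minus-baseline change has 51% power at 0.5 SD, slightly below the interaction. The gain needs both the average and the adjustment.

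**Conclusion.** The head-to-head analysis is not a wrong test and does not miss its stated power. It is an inefficient one that is hard to interpret. At 39 per therapy and ρ = 0.40, a baseline-adjusted mean of the two later scores raises power for a lasting 0.5 SD difference from 53% to 84% (75% under the 0.7 assumption), and from 85% to 99% at the planned 0.72 SD. The difference detectable with 80% power falls from 0.67 to 0.47 SD. It also gives one signed estimate with an interval. Most of the gain is baseline adjustment; dropping the second degree of freedom adds about 6 to 10 points under equal correlations.

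The conclusion rests on three assumptions: that the interaction is the intended term, that ρ = 0.40 carries over from the waitlist calculation, and that 39 children per therapy are analysed. The change is worth making, but nothing here invalidates the plan.

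**What to change.** - Define the EMDR v KIDNET test as the between-therapy difference in the mean of the post-treatment and 3-month CAPS-CA-5 severity scores, adjusted for the pre-treatment score, with a 95% CI. For children who come through the waitlist, those two assessments are T3 and T4.
- Report the baseline-adjusted difference at each of the two occasions, with CIs, as supportive results.
- Keep the three-occasion ANOVA as description.

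The cost is wording only, fixed before analysis begins. It needs no further participants or assessments. The article states that analysis waits for the final assessment.

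The downside is that the average is less sensitive to a purely temporary difference, and on its own it does not separate temporary from lasting effects. The occasion-specific estimates are needed for that.
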